## Abstract

**Background:**

Clavicle fractures account for around 4% of all fractures and up to 44% of fractures of the shoulder girdle. Fractures of the middle third (or mid-shaft) account for approximately 80% of all clavicle fractures. Management of this group of fractures is often challenging and the outcome can be unsatisfactory. In particular it is not clear whether surgery produces better outcomes than non-surgical management. Currently there is much variation in the use of surgery and a lack of good quality evidence to inform our decision.

**Methods/Design:**

We aim to undertake a multicentre randomised controlled trial evaluating the effectiveness and safety of conservative management versus open reduction and internal fixation for displaced mid-shaft clavicle fractures in adults. Surgical treatment will be performed using the Acumed clavicle fixation system. Conservative management will consist of immobilisation in a sling at the side in internal rotation for 6 weeks or until clinical or radiological union. We aim to recruit 300 patients. These patients will be followed-up for at least 9 months. The primary endpoint will be the rate of non-union at 3 months following treatment. Secondary endpoints will be limb function measured using the Constant-Murley Score and the Disabilities of the Arm, Shoulder and Hand (DASH) Score at 3 and 9 months post-operatively.

**Discussion:**

This article presents the protocol for a multicentre randomised controlled trial. It gives extensive details of, and the basis for, the chosen methods, and describes the key measures taken to avoid bias and to ensure validity.

**Trial Registration:**

United Kingdom Clinical Research Network ID: 8665. The date of registration of the trial is 07/09/2006. The date the first patient was recruited is 18/12/2007.

## Background

### Rationale for the trial

Clavicle fractures account for around 4% of all fractures [1] and up to 44% of fractures of the shoulder girdle [2,3]. Fractures of the middle third (or mid-shaft) account for approximately 80% of all clavicle fractures [2,3].

Management of mid-shaft clavicular fractures is often challenging and the outcome can be unsatisfactory. In particular it is not clear whether surgery produces better outcomes than non-surgical management. Traditionally mid-shaft clavicular fractures have been managed conservatively, even when substantially displaced [4].

Recent literature has highlighted the high non-union rate in displaced mid-shaft clavicular fractures, with a non-union rate up to 15% [5-7]. Furthermore, there is some evidence that conservative management affects the outcome in terms of upper limb function [8-10] and that treatment of non-unions produces inferior results [11,12]. Few comparative studies of surgical versus non-surgical treatment for mid-shaft clavicle fractures are available, and contradictory results have been obtained [13-15].

In a randomised controlled trial, though patients with mid-shaft clavicle fractures had higher functional scores at short-term follow-up after internal fixation, functional scores were similar at 6 months and 1 year. In addition, internal fixation with a modified Hagie pin was associated with a higher complication rate [13].

In a multicentre, prospective clinical trial [16], 132 patients with a displaced mid-shaft fracture of the clavicle were randomized to either operative treatment with plate fixation (67 patients) or nonoperative treatment with a sling (65 patients). Operative fixation of a displaced fracture of the clavicular shaft resulted in improved functional outcome and a lower rate of mal-union and non-union compared with nonoperative treatment at one year of follow-up. Hardware removal remained the most common reason for repeat intervention in the operative group.

A formal cost-effectiveness analysis based on the same prospective, randomized, controlled trial [14] proposed that the cost-effectiveness of open reduction and internal fixation (ORIF) after acute clavicle fracture depended on the durability of functional advantage for ORIF compared with nonoperative treatment. When functional benefits persisted for more than 9 years, ORIF had a favourable value compared with many accepted health interventions.

Two 2009 Cochrane reviews [1,11] on the management of middle third clavicle fractures concluded that there is insufficient evidence from randomised controlled trials to determine which methods of conservative [11] and surgical [1] treatment are the most appropriate for middle third clavicle fractures.

A 2010 systematic review [17] concluded that there is moderate evidence that operative treatment for mid-shaft clavicle fractures results in a lower rate of fracture non-union and improved patient-oriented outcome compared to non-operative treatment. However, because union rates are generally high and there are complications which are unique to surgical intervention, risks have to be considered before a decision on treatment is made. The most important risk factors for non-union are major displacement and fracture comminution. Of all surgical procedures the best evidence of efficacy is presently available for plate fixation and elastic stable intramedullary nailing [17].

### Trial aim

The aim of this multicentre randomised controlled trial (RCT) is to compare the safety and effectiveness of conservative and operative management of mid-shaft fractures of the clavicle in adults. The primary outcome will be the non-union at 3 months from injury. Secondary outcomes will be clinical scoring systems assessing pain, mobility, strength and function at 3 and 9 months follow-up.

Our null hypothesis is no difference in the non-union rate at 3 months from injury and in scoring systems at 3 and 9 months follow-up between the 2 groups.

## Methods/Design

### Study Design

This is a multicentre randomised controlled trial comparing safety and effectiveness of conservative management versus ORIF of mid-shaft clavicle fractures.

### Endpoints

The primary endpoint will be the rate of non-union at 3 months following treatment. Non-union is defined as lack of radiographic healing at 3 month follow up [16,18].

Secondary endpoints will be limb function measured using the Constant-Murley Score [19] and the Disabilities of the Arm, Shoulder and Hand (DASH) Score [20] measured at 3 and 9 months post-operatively.

### Ethical Considerations

#### Ethical approval

Ethical Approval has been obtained from the UK National Research Ethics Service, Charing Cross Hospital Ethics Committee (for multicentre trials) Reference number 06/Q0411/prior to commencement of this study. Local Ethics Committee approval for each unit involved in the trial will also be obtained.

#### Consent Procedures

Informed consent will be obtained from the patient prior to randomization.

Eligible patients will be provided with a patient information sheet and have the opportunity for discussion with a principal investigator at their first orthopaedic attendance. Patients will have up to a 24-hour period in which to seek further advice and reflect before inclusion.

#### Inclusion criteria

• Age 18-65 years

• Mid-shaft fracture of clavicle

• Robinson Classification 2B1 and 2B2 [21]

• Displaced mid-shaft fracture, butterfly fragment +/- comminution on radiographs

• Medically fit to undergo surgery (ASA grade 1-3)

#### Exclusion criteria

• Patient refusal

• Medically unfit (ASA Grade 4/5)

• All other clavicle fractures

• Established non-union from previous fracture

• Previous fractures around the clavicle

• Previous operations to shoulder or clavicle

• Metabolic bone disease

• Clinically important neuro-muscular upper limb disability.

#### Recruitment

Patients will be identified at attendance to the accident and emergency department at each hospital. They will be referred to fracture clinic, as this is the usual practice, and identified as eligible for the trial by the consultant surgeon in charge of the clinic.

It is estimated that in each centre approximately 2 patients per month will meet the inclusion criteria. It is also estimated that 80% of these patients will consent to be involved in the trial. Loss to follow-up will be small until 3 months, though for final follow-up and assessment is estimated a further 10% may be lost to follow-up.

#### Randomisation

Randomisation lists will be computer generated. Lists will be stratified by centre and blocked to ensure similar numbers of patients are allocated to the treatment groups within each centre. Allocations will be concealed in sequentially numbered opaque envelopes held at each site. 1 envelope will be opened for each patient. Eligible patients will be provided with a patient information sheet and consented using a trial consent form prior to randomisation.

#### Blinding

Because of the nature of the study it will not be possible to blind the patients or clinicians involved.

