The Constant-Murley [19] and Disability Arm Shoulder and Hand score (DASH) [20] scoring systems will be performed at the 3 month and 9 month reviews. The Constant-Murley score [19] is a practitioner completed objective score on a scale of 100 points divided into section for pain, activity, range of movement and strength and is measured for both arms. The Constant-Murley Score is one of the most used shoulder evaluation tool. This scoring system includes both physical examination tests and subjective evaluations by the patients allowing a functional assessment of the shoulder independently by the specific type of disorder. The Constant-Murley Score is divided into 4 subscales: Pain (15 points); Activities of daily living (ADL) (20 points); Range of Motion (ROM) (40 points) and Strength (25 points). The Pain and the ADL scales are self-reported by patients: in the first version of the Constant-Murley Score, the pain scale was scored as none (15 points); mild (10 points); moderate (5 points) and severe (0 points). In the revised version of 2008, the pain scale is scored by a VAS. The ADL score is divided into 4 items: Sleep, 2 points; Work and Recreational Activities/Sport 4 points each; Positioning the Hand in the Space, 10 points. ROM is evaluated as the active elevation of the arms on the sagittal and lateral planes and the internal and external rotation of the shoulders, 10 points each. Finally, strength is evaluated as the number of pounds of pull that the patient can resist in abduction to a maximum of 25 points. The total possible score is 100 points, indicating an asymptomatic and healthy person, while the worst score is 0 points. The validity and responsiveness of Constant-Murley Score were evaluated in successive studies [22]. Evaluating construct validity, the Constant-Murley Score showed strong correlation with other scales. Evaluating reliability, ICCs varied from 0.84 to 0.87.

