The DASH score [20] is a patient completed subjective score with 30 analogue scale responses producing a score between 0 and 100 points. The DASH score is a standardized questionnaire that assesses the symptoms and functional status in people with different upper extremity musculoskeletal disorders. The questionnaire consists of three sections: Symptoms, Sport and Music, Work. The first section is composed by 30 items and evaluates symptoms and functional status at the level of disability. The second and third sections are an optional module of four items for Sport and Music and four items for Work. Each item is scored with a five point scale: 1 = no difficulty; 2 = mild difficulty; 3 = moderate difficulty; 4 = severe difficulty; 5 = unable. The result of each module is summed and transformed to obtain the DASH score ranging, for each section, from 0 (no disability) to 100 (severe disability). Relatively to Internal Consistency the DASH has shown in multiple tests to have a high Cronbach's alpha (0.97); the responsiveness of the questionnaire (to self-rated or expected change) was comparable with or better than that of the joint-specific measures in the whole group and in each region [23].

An independent physiotherapy practitioner not involved in patient's surgical care or rehabilitation program will administer both assessment tools. There will a different examinator in each centre, who will be trained for the purpose of this study. The Constant score will be performed in a standardized way, using the same dynamometer in all the centres.

In the event of a patient developing a non-union at 12 weeks or more, he/she will exit the trial and be offered surgical management. Data regarding treatment offered and pursued will be collected.

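### No masking is provided for the independent physiotherapist who measures 65 of the 100 Constant-Murley points, so a powered secondary endpoint is open to detection bias

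*Protocol article*

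**What the plan says.** The Blinding section reads, in full: "Because of the nature of the study it will not be possible to blind the patients or clinicians involved". It names two groups and is silent on outcome assessors.

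The Assessment section says who scores function: "An independent physiotherapy practitioner not involved in patient's surgical care or rehabilitation program will administer both assessment tools". It then gives further safeguards: "There will a different examinator in each centre, who will be trained for the purpose of this study", and "The Constant score will be performed in a standardized way, using the same dynamometer in all the centres". Masking is not among them. The same section does use the word blinded, for the radiologist who re-reads the films of the first 40 patients, and of all patients if disagreement passes a stated limit.

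The Constant-Murley score is split into "Pain (15 points); Activities of daily living (ADL) (20 points); Range of Motion (ROM) (40 points) and Strength (25 points"). Of these parts, "The Pain and the ADL scales are self-reported by patients". Range of motion and strength are what the examiner measures.

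Operative Details specifies an infraclavicular incision. Endpoints names Constant-Murley as a secondary endpoint at 3 and 9 months, and Sample size gives it its own target difference, standard deviation and power.

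**The concern.** Patients and surgeons cannot be blinded to plate versus sling, and the Blinding section is right about that. The functional assessor is a different case. This person already exists, stands outside surgical care and rehabilitation, and could be kept from knowing the allocation. The plan stops at independence. Independence removes a personal stake in the patient's care. It does not remove an expectation about which treatment works better.

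Range of motion and strength depend on patient effort, and on how the examiner encourages, positions and reads. An examiner who sees a surgical scar can guess the arm. A systematic lean in those readings would shift the Constant-Murley difference between arms, and neither a larger sample nor intention-to-treat analysis would remove the shift. DASH is completed by patients who know their treatment, so masking the examiner cannot protect it. The examiner-measured part of Constant-Murley is therefore the part of the functional assessment that masking can protect.

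**Working it through.** **Step 1. Is masking planned?** Three places in the protocol article, side by side:
- Blinding: covers patients and clinicians only.
- Assessment, radiologist: described as independent and also blinded.
- Assessment, physiotherapist: described as independent, trained and using a standard dynamometer. Blinding is not mentioned.

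The authors use the two terms separately, and the Discussion paragraph of the abstract says the article sets out the main steps taken against bias. The fair reading is that no masking of the functional assessor is planned. No place says that the assessor is told the allocation.

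**Step 2. How much of the score is exposed?** From Assessment: range of motion 40 + strength 25 = 65 points measured by the examiner. Pain 15 + activities of daily living 20 = 35 points self-reported. Total 100.

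**Step 3. Reproduce the plan's own figure.** Inputs from Sample size: difference 5 points, SD 14.5, 150 per group, significance level 5% (taken as two-sided).
- SE = 14.5 × √(2/150) = 1.674.
- Power = Φ(5/1.674 − 1.96) = Φ(1.026) = 0.848. The stated power of at least 80% is reproduced.
- Recruitment allows for a further 10% loss by final follow-up: 150 × 0.90 = 135 per arm. SE = 14.5 × √(2/135) = 1.765, and power = Φ(5/1.765 − 1.96) = Φ(0.873) = 0.809.

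The concern changes no sample-size figure.

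**Step 4. What would a lean do?** The documents give no bias figure, so the lean b is an assumption. It means the net shift between arms, averaged over all centres, when there is no true difference. False-positive rate = Φ(b/SE − 1.96) + Φ(−b/SE − 1.96).

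| Net lean b | Share of 65 points | b/SE at 135 per arm | Rate, 135 per arm | Rate, 150 per arm |
|---|---|---|---|---|
| 0 | 0% | 0 | 5% | 5% |
| 1 | 1/65 = 1.5% | 0.567 | 8.8% | 9.2% |
| 2 | 2/65 = 3.1% | 1.133 | 20.5% | 22.3% |
| 3 | 3/65 = 4.6% | 1.700 | 39.8% | 43.3% |

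The 135 column fits the 9-month assessment. The plan expects little loss by 3 months, so the 150 column is nearer for that visit.

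**The case against.** The strongest reply is that the case rests on silence in a condensed article. The Blinding sentence is accurate for the people it names. Clothing, access to notes and instructions to patients could sit in a full protocol or site manual. This stands against the stronger reading that a reader might take from the text, namely that the physiotherapist scores with knowledge of treatment. The documents do not say so. It does not remove the point, because the article describes the functional assessment in some detail, lists its safeguards, and uses blinded for a different assessor in the same section.

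Other stronger readings also fail:
- A reader might infer that blinding was given up for the whole trial. The blinded radiologist shows otherwise.
- A reader might infer that covering the shoulders would hide the allocation. It can hide the scar. Unblinded patients can still disclose, especially as the same practitioner administers DASH and the self-reported Constant items.
- A reader might take the inflated error rates as a forecast. They follow from chosen leans and need those leans to run the same way across centres. There is a different examiner in each centre, with four sites recruiting and four more planned (Trial timeline), and leans in opposite directions would partly cancel.

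It is also fair to credit what is in place. Training, a common dynamometer and the same rehabilitation in both arms limit examiner variation and remove one cue to allocation. They do not hide the scar, and a dynamometer reading still depends on effort.

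Finally, the trial is already under way: the first patient was recruited in December 2007 and this protocol version dates from September 2010. A change now means that assessments are made under two procedures. That is a real cost and belongs with the fix.

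**Conclusion.** The point holds in limited form. The protocol makes no provision for masking the independent physiotherapist who measures 65 of the 100 Constant-Murley points, and the operative scar can reveal allocation. A secondary endpoint with its own power statement is therefore open to detection bias.

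The size is unknown. Under the assumption of a net lean of 1 to 3 points in one direction across centres, against a target difference of 5, the false-positive rate at 135 per arm would be about 9% to 40% in place of 5%. If leans cancel across centres, it stays at 5%.

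The reach is limited. The radiographic primary endpoint is not involved, and masking this examiner would do nothing for the 35 self-reported Constant points or for DASH. The point is worth acting on because the assessor is already separate from care and the remedy is cheap.

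**What to change.** Add to Blinding and Assessment that, for all remaining 3- and 9-month functional assessments and in both arms:
- both clavicles are covered by clothing;
- patients are asked beforehand not to disclose their treatment;
- the physiotherapist has no access to notes or radiographs;
- the physiotherapist records a guess of allocation after scoring.

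Record the date of the change at each site and report it with the Constant-Murley results, since earlier and later assessments will have been made under different conditions. If masking is already practised, the fix reduces to saying so and describing how.

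Cost: clothing, one line on the score form and a short briefing of examiners at each site, with no extra staff and no change to sample size or endpoints. Masking will help to conceal allocation but will sometimes fail, and the recorded guesses will indicate how often. Trial timeline foresees 18 more months of recruitment and 9 months of follow-up after that, so a substantial number of assessments can still benefit, and sites not yet open can start with the masked procedure.

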#### Baseline data collection

Baseline data will be collected on all patients before consent. These will include patient demographics, side of injury, mechanism of injury, fracture classification [21], ASA grade and whether the patient is a smoker. These data will be used to assess the balance in characteristics achieved by randomisation and also to compare the eligible group who declined to participate with the randomised group.

#### Operative Details

All procedures will be performed in an orthopaedic theatre under antibiotic cover according to local microbiology protocols in each centre. General anaesthetic will be used for all patients with or without supplementary interscalene blockade. All surgical procedures will be performed by one of the orthopaedic consultants named in the protocol or by their specialist registrar/research fellow under consultant supervision. All the patients enrolled in the study will be treated in a standardised way.

An infraclavicular incision will be used and a myo-periosteal flap elevated from the fracture segments. Fixation will be performed using the Acumed clavicle fixation system (Hillsboro, Oregon), consisting of a pre-contoured titanium plate with 2.7 mm or 3.5 mm screws. Image intensification will be available for all cases and hard copies will be obtained at the end of each procedure. Following wound closure the affected arm will be placed in an arm sling. Mobilisation and rehabilitation will be identical to the non-operative group (see below).

Data from the procedure will be documented on the operation note, including any peri-operative complications or deviations from the standard technique.

#### Non-operative Treatment

The arm on the fractured side will be immobilised in a sling at the side in internal rotation for 6 weeks or until clinical or radiological union. Pendulum and elbow exercises will be allowed the first day presenting in fracture clinic. Patients will be allowed to remove the sling for short periods to wash, dress, write, eat and use a keyboard as soon as comfort allows. Short-lever active and active-assisted exercises below shoulder height are allowed as tolerated. Active mobilisation above the horizontal and cross-arm adduction will be commenced after 6 weeks.

#### Post operative care

The same rehabilitation protocol will be used in patients undergoing surgical management, starting on the first day post-operatively.

#### Time-points

All patients will be followed up at 2 weeks, 6 weeks, 3 months and between 9 and 12 months from randomisation.

Patients will be given follow up dates at each appointment and a supplementary reminder letter will be sent to all patients before their 9 month appointment.

